#### Follow-up

We will follow-up both intervention and control groups for 6 months. We will evaluate feeding practices, such as feeding frequency, dietary diversity, and quality and quantity of food eaten by children, as well as nutrition status, on a monthly basis for six months. For the intervention arm, we will also measure nutrition knowledge of MLPs before the training, immediately after the nutrition training, and again after the six-month observation period in order to measure the degree of knowledge decay.

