#### Sample size estimation

To calculate the minimum sample size for the intervention and control group, we assumed the inter-cluster coefficient to be as low as 0.01. Also, we assumed that 8 clusters (CTCs) would be included in the intervention arm and a similar number in the control arm. We could not find any other studies, based in sub-Saharan Africa, that estimated weight gain after implementing this type of intervention, and therefore we used a similar study conducted in China investigating children in the general population as a reference [21]. In this study, an estimated mean weight gain difference between children of the intervention and control arm was 0.3 kg in six months. To detect the mean difference of 0.3 kg weight gained in the intervention group compared to the control group over a 6-month duration, at a power of 80% and 5% significant level, 24 participants per cluster will be needed. In total, a minimum sample size of 192 participants for each arm will be required to produce the desired effect. To counteract the effect of loss to follow-up, deaths, a number of outcome variables, and missing data, we will attempt to recruit 400 HIV-positive children for the intervention arm and a similar number for the control arm. Therefore, an estimated 800 caregivers will also be recruited to participate in this study, with a similar distribution between the intervention and control groups (400 in each arm).

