### Data analysis

We will analyze the data based on the intention-to-treat principle. We will use both descriptive and regression analyses. For the descriptive analyses, we will conduct both χ^2^ and Student’s *t*-tests to examine the differences in characteristics of participants in the intervention and control groups. This study will have two types of outcome variables. First, nutrition status measured as underweight, wasting, and stunting. Second, feeding practices measured by feeding frequency, dietary diversity, and the quality and quantity of foods consumed. We will use multiple logistic regression analyses to examine the effectiveness of nutrition training on nutrition status and feeding practices of the two arms while adjusting for confounding variables. We will also conduct analyses to see monthly changes in feeding practices and nutrition status and to compare the intervention and control arms. To examine the independent association of nutrition counseling by trained MLPs on outcome variables, we will use repeated measures of ANOVA and Generalized Estimated Equation.

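### Repeated measures ANOVA is named on equal terms with GEE for the monthly outcomes, yet in its standard form it drops any child with one missed month and does not suit the yes/no outcomes

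*Protocol article*

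**What the plan says.** The Data analysis section opens with the principle: "We will analyze the data based on the intention-to-treat principle". It defines two outcome groups. For the first it says: "First, nutrition status measured as underweight, wasting, and stunting". The second is feeding practices: frequency, diversity, and quality and quantity of food. Multiple logistic regression is named for both groups. For the effect of counseling by trained providers on the outcome variables, "we will use repeated measures of ANOVA and Generalized Estimated Equation". The section does not divide the outcomes between these two methods and does not rank them.

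The Follow-up section schedules feeding practices "as well as nutrition status, on a monthly basis for six months". With the separate Baseline assessment that makes seven time points, or six if only the monthly visits are counted.

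The Sample size estimation section sets a minimum of 192 children per arm and raises recruitment to 400 per arm. The reason begins: "To counteract the effect of loss to follow-up, deaths, a number of outcome variables, and missing data". It gives no rate for any of these losses.

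**The concern.** Standard repeated measures ANOVA needs a value at every time point. A child who misses one month, is lost late or dies leaves the analysis entirely, and the remaining values are discarded with that child. The result is a completers' comparison, which sits badly with the stated principle and with a recruitment margin meant partly to absorb missing data.

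The method also assumes a continuous outcome. Underweight, wasting and stunting are categories, and the Feeding frequency section cuts the count at five.

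GEE uses every available visit. With both methods named on equal terms, the same question may be answered on two different sets of children, with no rule for a disagreement. Precision is lost in the ANOVA. If attendance depends on growth differently in the two arms, the completers' comparison is also biased.

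**Working it through.** **The plan's own figure.** 8 clusters × 24 children = 192 per arm, which agrees with the text. The 24 cannot be re-derived because the SD of weight gain is not given. Working backwards from the stated inputs ("we assumed the inter-cluster coefficient to be as low as 0.01", a difference of 0.3 kg, 80% power, 5% level taken as two-sided):

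- Design effect = 1 + (24 − 1) × 0.01 = 1.23.
- Effective size = 192 / 1.23 = 156.1 per arm.
- Implied SD = 0.3 / (1.960 + 0.842) × √(156.1 / 2) ≈ 0.946 kg.

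The margin is 400 − 192 = 208 per arm, or 52% of those recruited.

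**Complete cases.** Let q be the share of visits missed per month (assumed) and k the number of time points that can be missed: 6 if every child has a baseline value, 7 if baseline can be missing too. With independent misses, complete cases per arm = 400 × (1 − q)^k.

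| q | k = 6 | k = 7 |
|---|---|---|
| 5% | 400 × 0.735 = 294 | 400 × 0.698 = 279 |
| 10% | 400 × 0.531 = 213 | 400 × 0.478 = 191 |
| 15% | 400 × 0.377 = 151 | 400 × 0.321 = 128 |

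**Rate at which 192 remain.** q = 1 − (192/400)^(1/k), which gives 11.5% for k = 6 and 10.0% for k = 7.

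**Misses clustered within children.** Independence is the harshest assumption here, since in practice some children miss often and most miss rarely. With a beta-binomial model and a within-child correlation of 0.3 (assumed), complete cases (k = 7 to k = 6) are 274 to 282 at 10%, 225 to 235 at 15% and 184 to 194 at 20%. The 192 minimum is then reached near 20%.

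**Precision.** Take independent misses, complete baselines and month-specific means. The complete-case variance of the six-month difference is the full-data variance divided by (1 − q)^6. An all-visits model cannot do better than full data, so the ratio of the two variances is at most 1/(1 − q)^6:

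- 5%: 1 / 0.735 = 1.36
- 10%: 1 / 0.531 = 1.88
- 15%: 1 / 0.377 = 2.65

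**Bias.** No size can be derived from the documents. It depends on how attendance relates to growth in each arm.

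**The case against.** The strongest reply is that the plan already names a suitable method. GEE uses all available visits and handles yes/no outcomes, and logistic regression is named too. ANOVA may be meant only for the z-scores, the dietary diversity score, the count of feeds and energy intake, where its outcome type fits. That stands in part: the outcome-type objection covers only the yes/no outcomes, and the text does not say ANOVA will be applied to them. The missed-month objection covers every outcome.

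A reader might infer that the plan breaks intention-to-treat. The article states no complete-case rule, and missing-data handling may sit in an analysis plan not shown. The conflict arises only if ANOVA is run in its standard form.

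A reader might also infer that the recruitment margin is used up. The documents do not support that. No missed-visit rate is given, the Study area section describes monthly attendance for ART refills, and at 5% missed the margin survives. The 192 is sized for six-month weight gain, which needs only baseline and month 6, so comparing it with children complete at every visit gives a yardstick, not a strict test.

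A claim that ANOVA would inflate false positives through unequal correlations between months would need the uncorrected test, and nothing says a correction will be omitted.

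Finally, ordinary unweighted GEE is not generally protected against drop-out that depends on observed weight. The bias argument therefore favors a likelihood-based model over ANOVA. It does not by itself favor GEE.

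**Conclusion.** The concern holds in a limited form. A method that in its standard form discards incomplete children is named on equal terms with one that does not, in a plan that promises intention-to-treat and expects missing data. It is a poor choice written into the text, so it is more than a detail left to a later document.

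The loss is conditional on an unstated missed-visit rate. It is modest at 5% (279 to 294 of 400 kept) and reaches the planned minimum at about 10.0% to 11.5% with independent misses, or near 20% with strong clustering of misses within children. The variance penalty is at most 1.36, 1.88 and 2.65 times at 5%, 10% and 15%, given independent misses, complete baselines and month-specific means. Bias is possible if attendance depends on growth differently by arm, but its size is unknown.

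The change is worth making because a better method costs almost nothing.

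**What to change.** In the Data analysis section, replace repeated measures ANOVA as follows.

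- **Continuous outcomes** (z-scores, weight, feeding counts, diversity score, energy): a linear mixed model on all available visits including baseline, with arm, month, arm-by-month, and random effects for CTC and child.
- **Yes/no outcomes** (underweight, wasting, stunting, low feeding frequency): a mixed logistic model, or the GEE already named, clustered on CTC with a small-sample correction because there are only 16 CTCs. Where drop-out related to observed growth is a worry, the mixed model is the safer of the two.
- **Precedence:** state that these are the deciding analyses and that every child is analysed in the arm of the CTC of enrolment. Keeping baseline in the model lets a child with no later visit still contribute.

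The cost is a few sentences, a covariance structure chosen in advance, and slightly more modelling work. No new data, visits or children are needed.

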### Ethical considerations

Before conducting interviews or allowing participation in the study, we will obtain written informed consent from the caregivers. Participants will be assured of the confidentiality and anonymity of reports and publications generated from this study. Participation will be voluntary and participants will be assured that there will be no implications for their care if they refuse to participate in the study. This study is approved by the Expedited Review Sub-Committee of the Senate Research and Publication Directorate of the Muhimbili University of Health and Allied Sciences in Tanzania and the Research Ethics Committee of the University of Tokyo in Japan.

## Discussion and implications

Nutrition training of health workers has been shown to be effective in improving the nutrition status of HIV-negative children. In our recent systematic review [10], health workers who were given in-service nutrition training could transform feeding practices and the energy intake of children in the general population. However, we could not find studies that targeted HIV-positive children. This population bears a higher burden of undernutrition compared to the general population. It is thus important to understand the effectiveness of such an intervention among this population.

Tanzania, along with other developing countries, also faces a shortage of well-trained health workers [6,51]. MLPs are left with the high burden of taking care of patients with minimum knowledge [8]. Our study will focus on the training of this health cadre and the examination of the efficacy of such training on management of undernutrition for HIV-positive children.

This study has the potential to directly transform the nutrition status and feeding practices of HIV-positive children in a region with a high burden of undernutrition. The findings of this study could support proposals to scale-up nutrition interventions using the available health infrastructure in semi-urban and rural areas of Tanzania, as well as in other countries with similar characteristics. We will also be able to better understand the local causes of undernutrition among HIV-positive children in an area that has adequate food production but a high toll of undernutrition.

The foreseen limitations of this study include differences in experiences and qualifications of targeted MLPs. Assistant medical officers have higher qualifications compared to clinical officers and assistant nurses. Their understanding of nutrition-related topics during the training might also be different. To minimize this limitation, we will use experienced trainers and both English and Swahili languages to emphasize the important points.

## Trial status

This trial was in the formulation phase during the preparation of this manuscript.

## Abbreviations

ART: Antiretroviral therapy; CTCs: Care and treatment centers; HFIAS: Household food insecurity access scale; MLPs: Mid-level providers; RCT: Randomized controlled trial.
